## Abstract

**Background:**

The acute effect of hemodialysis (HD) on left ventricular mechanics has been evaluated in several studies; however, their results are not consistent. Eventually, the heart and the arterial system behave as an interconnected system and not as isolated structures; thus, the evaluation of the interaction of cardiac contractility with the arterial system would provide a more comprehensive understanding of cardiovascular function and cardiac energetics. However, there have not been any studies demonstrating changes in terms of volumes, contractility, intraventricular pressure gradient distribution, and vascular properties in response to changes in loading conditions and their impact on the outcome in patients undergoing HD. Recently, a noninvasive method for assessing left ventricular pressure-volume loop and ventriculo-arterial coupling (VAC) from feature-tracking cardiac magnetic resonance or echocardiography has been proposed. We believe that this method allows a comprehensive evaluation of the hemodynamic status of the patients undergoing HD, including the relationships between cardiac function and arterial elastance, and might provide prognostic information.

**Objective:**

The primary objective of this study is to evaluate changes in VAC before and after a HD session. The secondary objective is to assess the prognostic value of VAC parameters in predicting adverse outcomes.

**Methods:**

A 2D transthoracic echocardiogram will be performed before and after a HD session in patients with end-stage renal disease. We target to enroll 323 patients. Images will be analyzed with advanced software based on speckle-tracking, able to reconstruct the pressure-volume loop. From the pressure-volume loop, arterial (Ea) and ventricular (Ees) elastance will be derived. VAC will be calculated as the Ea/Ees ratio. Patients will be followed up for 18 months. Primary endpoints will be a composite of all causes of death, nonfatal myocardial infarction, and hospitalization due to worsening heart failure.

**Results:**

The study received funding in August 2024, with patients’ enrollment scheduled to take place from January 1 to June 30, 2025. Data analysis will start in April 2025 and is expected to continue until June 2026. The findings of the study are tentatively planned for publication in the winter of 2027.

**Conclusions:**

This study will provide data on the changes in VAC induced by HD and their potential prognostic value. This assessment could be useful for tailoring volume depletion during HD and to improve patients’ outcomes.

**Trial Registration:**

ClinicalTrials.gov NCT06622928; https://clinicaltrials.gov/study/NCT06622928

**International Registered Report Identifier (IRRID):**

PRR1-10.2196/71948

## Introduction

### Background

One of the main goals of HD therapy is to remove from the patient the excess fluid that accumulates in the body due to kidney failure. Optimal fluid volume management is an essential component of HD adequacy, but the amplitude of volume fluctuation is still a quite challenging clinical condition. In fact, HD in patients with end-stage renal disease (ESRD) removes a large amount of fluid from the body in a few hours. Therefore, patients with ESRD on HD are characterized by central volume fluctuations related to volume expansion in the interdialytic period and fluid loss during HD. They also tend to have changes in cardiac structure and function, which have been recognized as key prognostic factors [1]. A myriad of mechanisms, such as chronic volume and pressure overload, anemia, uremia, high-flow arteriovenous shunts, fluid retention, abnormal calcium and phosphate metabolism, and hyperparathyroidism, can lead to cardiac abnormalities [2]. Furthermore, HD-induced acute hemodynamic changes in electrolytes, arterial pressure, blood volume, and sympathovagal balance can negatively impact cardiac function [3]. In fact, patients with chronic kidney disease exhibit a pronounced risk for cardiovascular events: 50% of all patients with chronic kidney disease stages 4 to 5 have cardiovascular diseases, and cardiovascular mortality accounts for approximately 40% to 50% of all deaths in patients with advanced chronic kidney disease (stage 4) as well as ESRD (stage 5), compared with 26% in controls with normal kidney function [4].

Changes in left ventricular (LV) volume during HD will alter LV contraction and strain. The acute effect of HD on echocardiographic indices of cardiac structure and function has been evaluated in several studies; however, their results are not uniform. Eventually, the heart and the arterial system behave as an interconnected system and not as isolated structures; thus, the evaluation of the interaction of cardiac contractility with the arterial system would provide a more comprehensive understanding of cardiovascular function and cardiac energetics. However, there is still scanty data on changes in volumes, contractility, intraventricular pressure gradient distribution, and vascular properties in response to changes in loading conditions and their impact on the outcome.

### Ventriculo-Arterial Coupling

The concept that the cardiovascular system works better when the heart and the arterial system are coupled has been well demonstrated [5-7]. When the heart pumps blood into the vascular tree at a rate and volume that matches the capability of the arterial system to receive it, both cardiovascular performance and its associated cardiac energetics are optimal [8]. A contractility or arterial tone that is too high or too low decouples these processes and can lead to cardiac failure independent of myocardial ischemia or the toxic effects of sepsis and related systemic disease processes. This optimization means that the LV workload and the arterial system optimally match when the LV ejects the blood into the arterial system and is quantified by ventriculo-arterial coupling (VAC) parameters. This process is optimized without excessive changes in LV pressure, and the mechanical energy of LV ejection is completely transferred from the ventricle to the arterial system [9].

VAC can be defined as the ratio of the arterial elastance (Ea) to the ventricular elastance (Ees). This ratio was first proposed by Suga and Sagawa [10] as a method to evaluate the mechanical efficiency of the cardiovascular system and the interaction between cardiac performance and vascular function. The Ea/Ees ratio has been consistently demonstrated to be a reliable and effective measure of cardiovascular performance [11]. The balance between myocardial oxygen consumption and the mechanical energy required to perform this work appears to be optimal when the heart and the peripheral vascular system are coupled (ie, the Ea/Es is near unity). In this case, the LV provides an adequate stroke volume with the lowest possible energetic consumption [12]. Thus, VAC is an effective index of the mechanical performance of the LV and the dynamic modulation of the cardiovascular system.

### Hypothesis and Study Aims

The relevance of VAC as a parameter of hemodynamic optimization could be related to the fact that VAC is a parameter of cardiovascular efficiency whereas the classical hemodynamic parameters are exclusively parameters of cardiovascular efficacy.

With these concepts in mind, the main scientific questions and hypotheses of this project are:

What is the impact of HD on ventricular function?What is the impact of HD on ventricular and arterial elastance?What is the prognostic value of intradialytic VAC changes?

Accordingly, we sought to study patients with ESRD to assess (1) VAC parameters before and after the HD session, and (2) the value of VAC parameters in predicting adverse outcomes.

## Methods

### Trial Design

This research is designed as an observational cohort study with a prospective approach. Participants will be enrolled and monitored over a period of time to assess how hemodynamic changes induced by HD influence future outcomes. As an observational study, the researchers will not intervene but will simply collect and analyze data as events occur naturally during the study period.

### Recruitment

Patients with ESRD undergoing permanent HD in a specialized center in Astana, Kazakhstan, will be recruited (Textbox 1).

Inclusion and exclusion criteria.
**Inclusion criteria**
Adults aged 18 years or older.Standard renal replacement schedule with 3 dialysis sessions per week.Dialysis vintage of at least 3 months.Dialysis adequacy with single-pool Kt/V >1.2 as recommended by international guidelines for thrice weekly HD.
**Exclusion criteria**
Previous kidney transplantation.Myocardial infarction, unstable angina, or stroke during the previous 6 months.Severe stage III to IV congestive heart failure according to the New York Heart Association classification.Chronic atrial fibrillation or other known arrhythmia.History of nonadherence to the prescribed weekly dialysis schedule in the previous month.BMI >40 kg/m^2^.History of malignancy or other clinical conditions associated with very poor prognosis.The main reasons for these criteria were to avoid confounding factors that may affect the hemodynamic parameters and to exclude patients with unstable conditions.

### Expected Outcomes

Patients will be followed up for 18 months. Clinical variables and intradialytic changes in VAC parameters will be related to outcome events. The primary endpoint will be a composite of all causes of death, nonfatal myocardial infarction, and hospitalization due to worsening heart failure. Based on previous studies, we expect a mortality rate of around 10% per year [13], an incidence of acute myocardial infarction of 3.9 per 1000 patients per year [14], and an incidence of hospitalization due to worsening heart failure of 5.8 per 100 persons per year [15].

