**2025**													
	Patient recruitment, informed consent, and data collection from eligible participants	✔	✔	✔	✔	✔	✔	✔	✔	✔	✔	✔	✔
	Data analysis (VAC)				✔	✔	✔	✔	✔	✔	✔	✔	✔
	1-year follow-up			✔	✔	✔	✔	✔	✔	✔	✔	✔	✔
	Manuscript preparation: (VAC)							✔	✔	✔	✔	✔	✔

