**2026**													
	Final data collection	✔	✔	✔									
	Data analysis (outcomes)	✔	✔	✔	✔	✔	✔						
	Manuscript preparation: (outcomes)							✔	✔	✔	✔	✔	✔

^a^IREC: Institutional Research Ethics Committee.

^b^VAC: ventriculo-arterial coupling.

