## Results

### Overview

At least 323 patients are required to estimate the incidence of cardiovascular events with 95% CI and a 5% margin of error. Data collection is scheduled to occur between January 1, 2025, and June 30, 2025. As of March 18, 2025, a total of 32 participants have been recruited, who underwent echocardiogram before and after the HD session. Data analysis is planned to start in April 2025 and continue through June 2026, with certain data being collected concurrently during the analysis phase. The publication of study outcomes is tentatively projected in Winter 2027.

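### The stated 18 months of follow-up does not fit the study's own calendar: no patient can reach it before data collection and analysis close, and expected outcome events fall by about 15% to 47%, depending on which stated dates hold

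*Protocol article*

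**What the plan says.** **Follow-up length.** Expected Outcomes states "Patients will be followed up for 18 months", and the Abstract (Methods) gives the same length. Table 1 has a 2025 row labelled "1-year follow-up", ticked from March to December 2025.

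**Enrolment window.** The Abstract (Results) has "enrollment scheduled to take place from January 1 to June 30, 2025". Results, Overview gives the same six months under another name: "Data collection is scheduled to occur between January 1, 2025, and June 30, 2025". Table 1 ticks the row "Patient recruitment, informed consent, and data collection from eligible participants" for all twelve months of 2025.

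**Close of data and analysis.** Table 1 ticks "Final data collection" for January to March 2026 and outcome analysis for January to June 2026, with the outcome manuscript from July 2026. Results, Overview agrees on the end of analysis: "Data analysis is planned to start in April 2025 and continue through June 2026". The same sentence adds that some data will still be gathered while analysis is under way. Publication is projected for winter 2027.

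**The concern.** Follow-up length sets the observation window of the composite of death, nonfatal myocardial infarction and heart failure hospitalization. The article calls this composite the primary endpoint, and the prognostic objective rests on it. If the calendar is followed, nobody is observed for the stated time. An 18-month event-free survival figure would then have no patients behind it, and fewer events would support the Cox and log-rank analyses. With 18 months, one year, March 2026 and June 2026 all on record, the outcome cut-off is also not fixed in advance.

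**Working it through.** **The plan's own figure.** Sample Size uses z = 1.96, P = 0.30 and E = 0.05. N = 1.96² × 0.30 × 0.70 / 0.05² = 322.7, rounded up to 323. This reproduces. The formula does not use follow-up time, so it neither supports nor corrects the 18 months.

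**Step 1: the calendar.**

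| Enrolled on | Reaches 18 months | Follow-up at 31 Mar 2026 | Follow-up at 30 Jun 2026 |
|---|---|---|---|
| 1 Jan 2025 | about 1 Jul 2026 | 14.9 months | 17.9 months |
| 30 Jun 2025 | about end Dec 2026 | 9.0 months | 12.0 months |
| 31 Dec 2025 | about end Jun 2027 | 3.0 months | 5.9 months |

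No entry in the last two columns reaches 18 months.

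**Step 2: event rate.** Expected Outcomes gives mortality of about 10% per year, myocardial infarction at 3.9 per 1000 per year and heart failure hospitalization at 5.8 per 100 per year. The article gives no composite rate. Summing is my assumption: λ = 0.10 + 0.0039 + 0.058 = 0.1619 per year, with a constant hazard and no dropout other than the closing date.

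**Step 3: full 18 months.** 1 − exp(−0.1619 × 1.5) = 0.2156, and 323 × 0.2156 = 69.6 events.

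**Step 4: events at a common closing date.** With uniform accrual, follow-up is uniform between a and b years, and the expected proportion with an event is 1 − [exp(−λa) − exp(−λb)] / [λ(b − a)]. For a = 0.75 and b = 1.25 this is 1 − (0.8857 − 0.8168)/0.08095 ≈ 0.149, or 48.2 events. The four combinations, in whole months, are:

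| Closing date | Enrolment closes | Follow-up (mean), months | Events | Change from 69.6 |
|---|---|---|---|---|
| 31 Mar 2026 | Jun 2025 | 9–15 (12) | 48.2 | −31% |
| 31 Mar 2026 | Dec 2025 | 3–15 (9) | 36.6 | −47% |
| 30 Jun 2026 | Jun 2025 | 12–18 (15) | 59.1 | −15% |
| 30 Jun 2026 | Dec 2025 | 6–18 (12) | 48.0 | −31% |

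Exact dates instead of whole months give 48.1, 36.4, 58.9 and 47.7 events.

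**Step 5: sensitivity to the rate.** I repeated this with mortality alone (0.10 per year), with the 10% treated as a yearly probability, and with a rate giving 30% by 18 months. For the March 2026 cut-off the loss stays at 30–32% (June close) and 47–49% (December close). For 30 June 2026 it stays at 15–16% and 31–32%. The absolute counts move: the full 18-month figure runs from about 45 events (mortality alone) to about 97 (30% by 18 months).

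**Step 6: what this means for precision.** As a yardstick, the hazard ratio per SD detectable with 80% power at two-sided 5% is about exp(2.80/√D). This gives 1.40 for D = 70, 1.44 for 59, 1.50 for 48 and 1.58 for 37. The article sets no power target, so these figures only compare scenarios.

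**The case against.** The date conflict itself is hard to dispute, because the ticked months in Table 1 agree with the prose on the start of analysis in April 2025 and its end in June 2026. The objections concern its size.

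- **Data collected during analysis.** The Overview allows some data to be gathered while analysis is under way. If that includes outcomes up to 30 June 2026, and enrolment closes in June 2025, the mean is about 15 months, the loss is about 15%, and the first possible patient misses 18 months by about a day. This stands, so the range must start there. It does not remove the conflict, because everyone enrolled later falls further short.
- **Enrolment to December.** The Table 1 row combines recruitment with data collection, so ticks after June may not mean enrolment, and the text twice gives 30 June 2025 as the end of the window. This also stands. The 47% loss holds only if the row is read as recruitment throughout.
- **Summed rates.** A patient hospitalized for heart failure who later dies counts once in the composite but twice in the sum, so about 70 events is nearer an upper bound if the component rates are right. The percentage losses hardly change.
- **Uniform accrual of 323.** This is assumed, and it is probably generous. The Overview reports 32 patients by 18 March 2025, which is 32 in 77 days or about 12.6 a month. At that pace 323 would take about 25.5 months.
- **Censoring.** Cox and Kaplan-Meier analyses accommodate staggered administrative censoring, so shorter follow-up costs precision and not validity. The Abstract lists prognosis as the secondary objective.
- **Publication in winter 2027.** This leaves calendar time, but analysis is stated to end in June 2026.

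**Conclusion.** The 18-month follow-up contradicts the article's own dates under every stated enrolment window and closing date. This conclusion needs no assumption.

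The loss of events is conditional. Against about 70 events at a full 18 months, it is about 31% (June close) or 47% (December close) with data collection ending in March 2026, and about 15% or 31% with outcomes collected to June 2026. These figures rest on summed rates, a constant hazard and uniform accrual of 323.

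A reader might infer that the study will certainly lose a third to a half of its events. The documents do not support that without condition: it needs the March 2026 cut-off, and the upper end also needs enrolment to December. Nor do they support the inference that the outcome analysis becomes invalid or that the whole study is undermined. The comparison of coupling before and after a dialysis session does not depend on follow-up. What suffers is precision for the prognostic objective, and any 18-month event-free survival estimate.

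**What to change.** Align the Abstract (Methods and Results), Expected Outcomes, Table 1 (2025 and 2026) and Results, Overview on one enrolment window and one outcome closing date. There are two ways to do this.

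1. **Keep the 2026 close.** Replace both the 18 months and the one-year label with a common closing date and the follow-up range it gives: for example 9–15 months for 31 March 2026, or 12–18 months for 30 June 2026, with enrolment closing in June 2025. Restate the expected events with their assumptions, and report event-free survival only to a time that most patients have reached. This changes text and no procedures, but accepts fewer events.
2. **Keep the 18 months.** Collect outcomes until 18 months after the last enrolment: about end December 2026, or mid-2027 if enrolment runs to December 2025. Correct the one-year row and start outcome analysis after that date. Table 1 starts it in January 2026, so the start moves by about 12 or 18 months. The end of data collection moves from March 2026 by about 9 or 15 months. The article describes no repeat echocardiogram during follow-up, so the cost is time and continued event ascertainment.

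Under Ethical Considerations, important protocol modifications go to the ethics committee, so either change may need submission. The choice should be fixed before outcome data are examined.

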### Participant Timeline

The schedule of the study project including enrolment and assessment is outlined in Table 1.

**Table 1 table1:** Schedule of the study project from 2024 to 2026.

Events		January	February	March	April	May	June	July	August	September	October	November	December
**2024**													
	IREC^a^ approval							✔					
	Hiring research assistants								✔				
	Logistic set-up (workstation, software, training with Medis imaging bioengineering)									✔	✔	✔	✔
	Checklist (VAC^b^)									✔	✔	✔	✔
	Manuscript preparation (review)								✔	✔	✔	✔	✔
**2025**													
	Patient recruitment, informed consent, and data collection from eligible participants	✔	✔	✔	✔	✔	✔	✔	✔	✔	✔	✔	✔
	Data analysis (VAC)				✔	✔	✔	✔	✔	✔	✔	✔	✔
	1-year follow-up			✔	✔	✔	✔	✔	✔	✔	✔	✔	✔
	Manuscript preparation: (VAC)							✔	✔	✔	✔	✔	✔
**2026**													
	Final data collection	✔	✔	✔									
	Data analysis (outcomes)	✔	✔	✔	✔	✔	✔						
	Manuscript preparation: (outcomes)							✔	✔	✔	✔	✔	✔

^a^IREC: Institutional Research Ethics Committee.

^b^VAC: ventriculo-arterial coupling.

### Sample Size

The sample size was calculated based on 95% CI, margin of error 5%, and estimated incidence of cardiovascular events 30%, as follows:

[figure not shown]

where N is the sample size, 
[figure not shown]
 is a critical value from the standard normal distribution corresponding to the desired 95% CI (1.96), *P* is the proportion of estimated incidence (0.3), and E is the desired margin of error (0.05) [16].

### Feasibility of Recruitment of the Sample Size

Patients on HD are often fragile and may not accept to undergo an additional investigation, although noninvasive. We will try to limit the number of noncompliant patients with several actions (Textbox 2).

Action plan to reduce the number of uncompliant patients.Involvement of the referring nephrologist in the explanation of the study.Clear explanation to the patient on the nature of a transthoracic echocardiogram (Multimedia Appendix 1).Patients are coming 3 times per week; thus, we will give them the freedom to choose any appropriate day for the study.We will provide a summary of the echocardiographic study to the dialysis center to be shared with the patients.

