### Echocardiography

2D and Doppler echocardiogram will be acquired by a skilled sonographer before and immediately after the HD session. Care will be taken in acquiring 2D apical views (4-chamber, 2-chamber, and long-axis views) aiming for the best visualization of the LV endocardial border. Images will be saved on digital media storage devices and analyzed offline at the echocardiographic core laboratory of our institution.

Echocardiographic images will be analyzed offline using dedicated software based on a mathematical model [18] (QStrain, Medis BV). The LV end-diastolic and end-systolic volumes and ejection fraction will be determined from the modified biplane Simpson method. Left atrial volume will be calculated using the biplane area-length method. LV volume and mass and left atrial volume will be subsequently indexed by body surface area. The peak early filling (E wave), the late diastolic (A wave) velocities, and the deceleration time will be assessed from the transmitral flow. The peak systolic (s’), early diastolic (e’), and late diastolic (a’) mitral annular velocities will be measured at the septal annulus using spectral Doppler.

LV volumes, estimated end-diastolic pressure, and brachial systolic and diastolic pressures will be used as input. The software reconstructs the pressure-volume (P-V) loop by determining the end-systolic pressure-volume relationship (ESPVR) and end-diastolic pressure-volume relationship (EDPVR) using the single-beat algorithms previously described in the literature [19]. Once the EDPVR and ESPVR are identified, the end-diastolic and end-systolic LV volumes and systolic and diastolic brachial pressures will be used to close the P-V loop. Finally, the P-V relation will be depicted for the entire cardiac cycle where each point of the curve is described as (Vt, Pt). In the P-V loop, the classic phases of the cardiac cycle are displayed: isovolumetric contraction, ejection, isovolumetric relaxation, and diastolic filling (Figure 2).

Based on this integrated P-V loop, the hemodynamic parameters to be calculated, both before and after the HD session, are listed in Textbox 3.

The pre- and posthemodialysis changes will be calculated and considered as potential prognostic indicators.

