### Statistical Analyses

Statistical analysis will be performed with Statistical Package Stata (StataCorp) and R-studio (Posit). All continuous variables will be presented as mean (SD) or median (IQR) based on their distribution. Paired comparisons of continuous variables will be performed with a 2-tailed paired Student *t* test or Wilcoxon test, when appropriate. Paired comparisons of categorical variables will be conducted with the McNemar test. Event-free survival for each of the echocardiographic and VAC parameters will be assessed using Kaplan-Meier analysis and compared with a log-rank test, where each index will be dichotomized according to the median of its distribution. The prognostic value will be determined using the Cox proportional hazards model. Differences will be considered statistically significant when *P*<.05. Interclass correlation coefficients (ICC) will be calculated to assess the inter- and intraobserver agreement of P-V loop measurements.

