Sasso et al [33] evaluated 15 patients on HD. They concluded that HD influences both Ees and Ea/Ees ratio acutely, although this effect seems due only to the acute reduction in preload and blood pressure, without any clinically significant effect on intrinsic LV contractility and VAC. In a study on 234 HD patients, Obokata et al [34] found that Ea/Ees ratio was independently associated with adverse outcomes, providing an incremental prognostic value over the clinical score and left ventricular ejection fraction. Recently, Zuo et al [35] used an approach similar to ours (pre- and posthemodialysis assessment of VAC). They concluded that VAC is a reliable index for stratifying the risk of cardiovascular diseases in HD patients.

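### Free choice of dialysis day mixes short and long interdialytic intervals, so the ranking of patients by VAC change partly reflects the session chosen, and the described analysis does not account for it

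*Protocol article*

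**What the plan says.** The inclusion criteria require a "Standard renal replacement schedule with 3 dialysis sessions per week". Under Feasibility of Recruitment of the Sample Size, one of the steps to limit refusals is: "Patients are coming 3 times per week; thus, we will give them the freedom to choose any appropriate day for the study". What makes a day appropriate is not defined.

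The measurement is tied to one session: "2D and Doppler echocardiogram will be acquired by a skilled sonographer before and immediately after the HD session" (Echocardiography). The same section gives the change a second use: "The pre- and posthemodialysis changes will be calculated and considered as potential prognostic indicators".

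In Statistical Analyses, pre and post values are compared with a paired t test or Wilcoxon test. For Kaplan-Meier and log-rank, "each index will be dichotomized according to the median of its distribution". Then: "The prognostic value will be determined using the Cox proportional hazards model". The interval before the studied session is not mentioned in any of these steps.

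Two other places bear on why the interval matters. The Background describes "central volume fluctuations related to volume expansion in the interdialytic period and fluid loss during HD". Comparison to Previous Work cites a 15-patient study of the acute change in Ees and Ea/Ees, which concluded that "this effect seems due only to the acute reduction in preload and blood pressure".

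**The concern.** The protocol's own account is that volume builds up between sessions and is removed during HD, and it cites work attributing the acute change in Ea/Ees to the fall in preload and pressure. On that account, the time since the last session helps determine the quantity being measured. The eligibility criteria were chosen to keep out factors that disturb the hemodynamic parameters; the free choice of day lets one back in.

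Two results are affected. The average VAC change depends on how many patients happened to choose the session after the long gap, so it is hard to compare with another cohort that has a different mix. More importantly, two patients with the same cardiovascular response can land in different halves of the median split because they were studied on different days. A log-rank comparison of those halves, as described, does not correct for this.

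**Working it through.** **The plan's own figure.** The sample size uses z = 1.96, P = 0.30 and E = 0.05: N = 1.96² × 0.30 × 0.70 / 0.05² = 322.69, rounded up to 323. This reproduces. The session day does not enter the formula, so N is not affected by this point.

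**Is mixing unavoidable under free choice?** Three sessions on separate days of a seven-day week can be spaced only as 2-2-3, 1-3-3, 1-2-4 or 1-1-5 days. None is even. The most even, 2-2-3, has one session in three after a longer interval. The protocol does not write out this pattern; it follows from the calendar.

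**How much could it matter?** The documents give neither the effect of the interval on VAC change nor the expected mix of days, so both are assumptions here:

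- The patient's own response c is standard normal (between-patient SD = 1).
- A share q of patients is studied after the long interval.
- The long interval adds d, in between-patient SDs, so the observed change is c + d for long-interval patients and c for the others.

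Formulas:

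- Share of between-patient variance due to the day: d²q(1−q) / [1 + d²q(1−q)].
- The observed median m solves (1−q)Φ(m) + qΦ(m−d) = 0.5.
- Share of patients on the other side of the median from where c alone would put them: 2q[P(high | long) − 0.5], with P(high | long) = 1 − Φ(m−d).
- Shift of the cohort mean: q × d.

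Results at q = 1/3:

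| d (SD) | variance due to day | high half, long interval | high half, short interval | other side of median | of 323 | mean shift (SD) |
|---|---|---|---|---|---|---|
| 0.2 | 0.9% | 55% | 47% | 3.5% | 11 | 0.07 |
| 0.5 | 5.3% | 63% | 43% | 8.7% | 28 | 0.17 |
| 0.8 | 12.5% | 71% | 40% | 13.7% | 44 | 0.27 |
| 1.0 | 18.2% | 75% | 37% | 16.8% | 54 | 0.33 |

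Worked line for d = 0.5: m = 0.165; P(high | long) = 1 − Φ(0.165 − 0.5) = 0.631; 2 × (1/3) × (0.631 − 0.5) = 0.087; 0.087 × 323 = 28.

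Over q = 1/6 to 1/2 and d = 0.2 to 1.0, the share on the other side of the median runs from 2.2% to about 19%. If every patient were studied after the same interval, it would be zero.

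**The case against.** Several objections are fair, and some of them limit the point.

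- **The paired comparison.** Each patient is their own control within one session. A reader might infer that the pre/post test is biased. It is not: an average over ordinary sessions is a legitimate target, and only its mix is uncontrolled. Nor is it a defect that the test cannot separate HD from fluid removal, since the study question is the impact of HD and fluid removal is part of HD.
- **The Cox model.** A reader might infer that it is univariable. The article does not say so. Expected Outcomes says that clinical variables as well as VAC changes will be related to events, and a covariate list may stand in a fuller document. What the text does show is a median-split log-rank comparison with no adjustment.
- **Data capture.** Dialysis-related parameters go onto a case report form that is not shown, so ultrafiltration volume may already be recorded. The word appropriate might also hide a restriction, but nothing shown says that it fixes the interval.
- **The cited small study.** It also found no clinically significant effect on intrinsic contractility and VAC. It supports load dependence of the measured ratio, not a VAC change proportional to the fluid removed. Scaling the change by 3/2 for a three-day against a two-day gap therefore has no basis in the documents.
- **Confounding.** A reader might infer that sicker patients choose particular days. The article calls HD patients often fragile, but it does not link health to choice of day.

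None of this removes the mixing of intervals or its effect on the ranking.

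**Conclusion.** The point stands as an avoidable source of variation in the patient-level VAC change. The mixing of intervals follows from the thrice-weekly schedule and the stated freedom of choice; its relevance follows from the protocol's own account of volume and preload. The paired test is unaffected in validity, and the main harm is to the between-patient ranking used for prognosis. The expected result is noise and attenuation of a prognostic association. Confounding would need a link between day choice and prognosis, which the documents do not show.

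The size is uncertain. At the low end of the assumed range (0.2 SD) about 3.5% of patients change side of the median and the problem is minor; at 1.0 SD it is about 17%. These figures rest on a normal response, a constant day effect and one third of sessions after the long interval. The correction is worthwhile because it costs almost nothing, not because a large bias has been shown.

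**What to change.** 1. For every studied session, including the 32 patients recruited by March 18, 2025, derive the preceding interdialytic interval (short or long) from the session date and the patient's schedule. Because recent nonadherence to the schedule is an exclusion, the schedule should be a reliable basis for this.
2. Keep the paired test, and report the VAC change separately for short and long intervals with the number in each.
3. Add a regression of post-HD Ea/Ees on pre-HD Ea/Ees with interval as a covariate.
4. Include interval in the Cox model of the VAC change, and stratify the log-rank comparison by interval. Within a stratum the interval is the same for all, so the comparison no longer reflects it.
5. Report a model with ultrafiltration volume relative to body weight only as secondary and explanatory. It lies on the pathway of the HD effect, so adjusting for it in the main model would change the question.

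Patients keep their free choice of day. Limiting new patients to short-interval sessions is not needed; it would weaken a measure meant to help recruitment and leave out one kind of session. The cost is one derived variable, one extra model term and slightly more analysis. The sample size stays at 323 and dialysis care is untouched.
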